### Referral to lower intensive services/primary care

Through administrative records it will be assessed to which extent patients are referred to lower intensive services, most likely primary care.

### Therapeutic relationship

The STAR (Scale To Assess the Therapeutic Relationship) [39] is a 12-item instrument that measures the quality of the therapeutic alliance between patients with severe mental illness and professionals. It is administered both by patients (STAR-P) and professionals (STAR-C), and has good psychometric properties.

The DDPRQ (Difficult Doctor Patient Relation Questionnaire) [40] is a 10-item instrument that assesses problems in the relationship between patient and professional and the perceived difficulty with very good psychometric properties.

### Care needs

The CANSAS (Camberwell Assessment of Need Short Appraisal Schedule) [22] is the single most used care needs assessment instrument among people with severe mental illness. Both the patient’s perception (through an interview by the researcher), and the professional’s perception (self-rated) are assessed through a 22-item checklist that measures met, unmet, and total needs for care.

### Social network

The Social Network Map (SNM) [41] is a researcher-assessed instrument using both a graphical (map) and textual (grid) instrument to assess the patient-perceived quantity and quality of his or her social network. The map is divided into sectors (household, other family, work/school, formal services, friends, neighbours, and clubs/organizations/church). The psychometric qualities of the instrument, as in all social network instruments, are acceptable.

### Statistical analyses

The primary outcome will be analysed using a linear mixed model (multilevel) to account for the nesting of clients within professionals and for the correlation over time of repeated measurements within subjects. The effect of ICPT versus CAU will be adjusted for important client and professional characteristics (e.g. quality of life) by including the latter as fixed effects in the model. Similar mixed models will be used to analyse the continuous secondary outcomes. All analyses will be performed on an intention-to-treat basis.

### Health economic evaluation

This study will investigate the potential efficiency of Interpersonal Community Psychiatric Treatment (ICPT) versus current long-term care (CAU) from a societal perspective. The economic evaluation will be based on the general principles of a cost-effectiveness analysis as described by Drummond et al. [42] and will be performed along-side the (cluster randomized) clinical trial. Outcome measures for the economic evaluation, considering the 18-months follow-up period, will be costs, quality of life and quality adjusted life years (QALYs). The cost analysis exists of three main parts.

First, on patient level, volumes of care will be measured prospectively using TiC-P (part I), administrative data. Cost items included are: number of outpatient contacts, home visits, number and length of hospitalizations, but also ER/casualty department-visits, ambulance transportation, and justice department contacts. Productivity losses for patients (sick leave) will be estimated using TiC-P part II. The friction cost-method will be applied following the Dutch guidelines for cost analyses [43]. Also travel time to an outpatient clinic and related costs patients make, will be considered. Second, the cost analysis consists of determining the cost prices for each volume of consumption in order to use these for multiplying the volumes registered for each participating patient. The Dutch guidelines for cost analyses will be used [44]. For units of care/resources where no guideline or standard prices are available real cost prices will be determined. Third, per arm (intervention and control) total costs will be determined using activity based costing. The effect analysis adheres to the design of a randomized controlled trial and measures at baseline, and follow-ups at 6, 12 and 18 months. To measure the quality of life of patients a validated so-called health-related quality of life (HRQoL) instrument will be used, the EuroQol-5D (EQ-5D) [45].

The incremental cost-effectiveness ratio’s (ICERs) ‘cost per unit change on the MANSA’ and ‘cost per QALY gained’ will be computed and uncertainty surrounding these ICERs will be determined using the bootstrap or Fieller method. Cost-effectiveness acceptability curves will be derived that are able to evaluate efficiency by using different thresholds (Willingness To Pay) for a unit change on the MANSA and a QALY gained. The impact of uncertainty surrounding deterministic parameters (for example prices) on the ICER will be explored using one-way sensitivity analyses on the range of extremes.

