**Methods/Design:**

Multi-centre cluster-randomized clinical trial: 36 professionals will be randomly allocated to either ICPT or CAU for an intervention period of 12 months, and a follow-up of 6 months. 180 Patients between 18–65 years of age will be included, who have been diagnosed with a non-psychotic psychiatric disorder (depressive, anxiety, personality or substance abuse disorder), have long-term (>2 years) or high care use (>1 outpatient contact per week or >2 crisis contacts per year or >1 inpatient admission per year), and who receive treatment in a specialized mental health care setting. The primary outcome variable is quality of life; secondary outcomes are costs, recovery, general mental health, therapeutic alliance, professional-perceived difficulty of patient, care needs and social contacts.

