### Sample size calculation

This study’s sample size calculation is based on the primary outcome variable, quality of life as measured with the Manchester Short Assessment of Quality of Life (MANSA), for which we found an effect size of 0.3 in our pilot study [17]. In a patient group in which quality of life is difficult to improve, an effect size of 0.3 signifies clinically meaningful progress. Furthermore we assumed a conservative Intra Cluster Correlation of 0.10 for clustering of patients, based on the scarce literature on the correlation between long-term psychiatric patients within one professional [17]. The correlation between baseline and follow-up measurement, also from our pilot study, was set at 0.5 and 0.8 for cluster and subject level, respectively. With an alpha of 0.05, and a power of 0.80, 36 clusters (professionals) of 5 participants (patients) each are required (total of 36 professionals and 180 patients needed for the analysis).

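### The plan does not tie ICER uncertainty and acceptability curves to the randomised unit; standard patient-level bootstrap or Fieller methods would overstate precision

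*Protocol article*

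**What the plan says.** Professionals are the randomised unit: the abstract says that "36 professionals will be randomly allocated to either ICPT or CAU". The Sample size calculation section says that "36 clusters (professionals) of 5 participants (patients) each are required", and for the MANSA that "we assumed a conservative Intra Cluster Correlation of 0.10 for clustering of patients".

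The Statistical analyses section gives the primary outcome a linear mixed model, in part "to account for the nesting of clients within professionals", and extends similar models to the continuous secondary outcomes. The abstract lists costs among the secondary outcomes.

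The Health economic evaluation section says that the evaluation "will be performed along-side the (cluster randomized) clinical trial". It defines two ICERs, cost per unit of MANSA change and cost per QALY, and says that "uncertainty surrounding these ICERs will be determined using the bootstrap or Fieller method". Acceptability curves over a range of willingness-to-pay thresholds follow. The section names no resampling unit, no variance estimator for Fieller's method, and no step by which the professional enters the ICER intervals or the curves.

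**The concern.** The clinical and economic analyses use the same patients under the same professionals, but only the clinical section says how clustering is handled. For the MANSA ratio the mismatch is direct, because its denominator is the outcome for which the plan itself assumes an ICC of 0.10.

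In its usual form the bootstrap resamples patients, and Fieller's method uses patient-level variances and a patient-level covariance. Applied that way in a cluster-randomised trial with positive ICCs, both give intervals that are too short. They also push the acceptability curve away from 50%, so that a chance difference between two groups of professionals looks more convincing than it is. Costs are part of the stated research aim, and greater cost-effectiveness is one of the hypotheses. The economic conclusion should therefore rest on the same unit of inference as the clinical one.

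**Working it through.** **Inputs.** Cluster size m = 5 and 36 clusters, so 36 × 5 = 180 patients (Sample size calculation). ICC = 0.10, given there for the MANSA only. The article states no ICC for costs or QALYs and no precision figure for the ICERs or curves, so there is no planned figure to reproduce. ICCs of 0.01, 0.05 and 0.20 are assumptions added to show a range. Equal allocation, 18 professionals per arm, is assumed for the simulation.

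**Where clustering enters.** At willingness to pay λ, the incremental net benefit is NB = λΔE − ΔC, and the curve is approximately Φ(NB/SE). Fieller's limits are the values R that solve (ΔC − RΔE)² = z²(V_C − 2R·V_CE + R²·V_E). If costs, effects and their covariance share one ICC, all three variance terms grow by the same design effect, DE = 1 + (m − 1) × ICC. A patient-level calculation leaves that factor out.

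**At ICC 0.10.**
- DE = 1 + 4 × 0.10 = 1.40, and √1.40 = 1.183.
- Patient-level SE divided by correct SE = 1/1.183 = 0.845, an understatement of about 15%.
- Coverage of a nominal 95% interval = 2Φ(1.96/1.183) − 1 = 90.2%, an error rate of about 10% instead of 5%.

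**Range by assumed ICC, same formulas.**

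| ICC | DE | SE understated by | Coverage of nominal 95% |
|---|---|---|---|
| 0.01 | 1.04 | 1.9% | 94.5% |
| 0.05 | 1.20 | 8.7% | 92.6% |
| 0.10 | 1.40 | 15.5% | 90.2% |
| 0.20 | 1.80 | 25.5% | 85.6% |

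**Acceptability curve.** A patient-level probability p corresponds to Φ(z_p/√DE) once clustering is allowed for. At ICC 0.10, 0.95 becomes Φ(1.645/1.183) = 0.92, and 0.90 becomes Φ(1.282/1.183) = 0.86. At ICC 0.05 they become 0.93 and 0.88.

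**Simulation check.** The set-up was 1,500 trials of 18 + 18 professionals with 5 patients each, a normally distributed net benefit, ICC 0.10, and a percentile bootstrap with 400 resamples. Resampling patients covered 89.5%; resampling professionals covered 93.4%. The Monte Carlo standard error near 90% is √(0.9 × 0.1/1500), about 0.8 percentage points, so the first figure agrees with the formula. The cluster bootstrap also falls a little short of 95%. With 18 clusters per arm its standard error is low by about √(17/18) = 0.972, which is small beside the patient-level shortfall.

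**The case against.** The strongest reply is that the article does not say what the concern fears. It never calls the bootstrap patient-level, and both named methods can respect clusters, by resampling professionals or by feeding Fieller's method with multilevel variances. The economic section itself calls the trial cluster randomised, and the Discussion says that the data are clustered at several levels. Costs are a listed secondary outcome, so the mixed models for continuous secondary outcomes may cover mean costs. The resampling unit is also the kind of detail that a condensed article may leave to a fuller document.

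Much of this stands. A reader might infer that the plan uses a patient-level bootstrap and that its intervals will be too narrow. The text does not support that; it leaves the unit open. A reader might also infer that costs cluster at least as strongly as the MANSA because professionals drive service use. The article gives no ICC for costs. Its cost items include hospital stays, emergency visits, ambulance transport, justice contacts and sick leave, which a single professional need not determine. At an ICC of 0.01 the loss would be negligible.

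The objection does not remove the point. The economic section does more than stay silent: it names a separate method for the ICERs and curves, and the standard form of that method assumes independent patients. Nothing carries the mixed-model variances into those intervals or curves. Mixed models for mean costs would not do so by themselves, because the ratio also needs the cost-effect covariance, and QALYs appear as an outcome only in the economic evaluation.

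**Conclusion.** The point holds in conditional form. The plan names methods for ICER uncertainty without linking them to the randomised professionals, although it makes that link for the clinical outcomes. If the standard patient-level form were used, precision would be overstated. At 5 patients per professional and ICC 0.10 the standard error would be about 15% too small and coverage about 90%; across ICCs of 0.01 to 0.20, coverage would run from about 94.5% to 86%.

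These figures assume equal cluster sizes, approximate normality, and one ICC for costs, effects and their covariance. The 0.10 comes from the MANSA; applying it to costs or QALYs is an assumption. The size is moderate, but for any positive ICC the direction is towards overconfidence. The documents do not show that the intervals will in fact be too narrow.

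**What to change.** Amend the sentence on ICER uncertainty in the Health economic evaluation section so that it names the unit. Either of two routes would serve:

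- Bootstrap by resampling professionals within arm, and within any randomisation strata, keeping each patient's cost-effect pair together. The Randomization section mentions stratification without naming the factors, so the wording should refer to whichever strata were used.
- Estimate incremental cost and effect jointly in a bivariate mixed model with a random professional effect.

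Derive both ICER intervals and both acceptability curves from the chosen route. Use Fieller's method only with cluster-adjusted variances and covariance.

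The cost is a short amendment, slightly more analysis work and somewhat wider intervals (by a factor of about 1.18 at ICC 0.10, less at lower values). No extra patients or data are needed.

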## Discussion

No RCT, nor cost-effectiveness study, has been conducted on Interpersonal Community Psychiatric Treatment so far – only one, small pilot study, promising better outcomes than in usual care. The empirical base for current care as usual is small, if not absent. This study will fill this void, and generate data that is needed to inform and hopefully improve daily mental health care. In summary, we assume that ICPT is more effective in improving patients’ quality of life and social networks, preventing or decreasing professionals’ perception of patients as ‘difficult’, discharging patients to a lower level of care and being less costly in reaching these clinical goals than CAU. The patient group we focus on, receives long term care and suffers from various non-psychotic psychiatric diagnoses. The strength of ICPT is its focus on this varied group of patients, for whom current care is unsatisfactory.

The rationale performing a cluster-randomized design is threefold. First: data from this trial will be clustered at multiple levels, due to three participating institutions, various departments within these institutions, and various professionals (=cluster level) within these departments. Second: contamination of treatment methods is likely when professionals treat patients in both the experimental and control condition. Contamination is less likely in the current design since participating professionals have limited contact on treatments or methods with one another outside official treatment progress meetings – in which there is little time to discuss treatment content. Therefore randomization at the level of professionals is preferable. Third: refusal to be randomized is likely with this patient group. Many patients find it difficult to switch to another professional since they may have a long-term working alliance with their present professional. Randomization therefore takes place on the professional level instead of on patient level.

It is expected that this study will yield results that may well be generalized across everyday mental health care. Since our target population consists of patients who are high care users, who are more willing to participate than patients who receive for example assertive outreach [9], we do not expect high selection bias. There are a limited number of inclusion and exclusion criteria in our trial. Unlike in many other trials, patients who are suicidal, aggressive, or self-harming are welcome to participate. Also, comorbidity as well as substance abuse are no exclusion criteria. To encourage participation by professionals, a tailored training-program was developed, based on their day-to-day work with the participants involved. A limitation of this study is the lack of blinding. Participating professionals will know that they conduct ICPT instead of CAU. Patients will also not be blinded.

## Abbreviations

CANSAS: Camberwell Assessment of Need Short Appraisal Schedule
CAU: care as usual
DALY: Disability-adjusted life years
DDPRQ: Difficult Doctor Patient Relation Questionnaire
EQ-5D: Europol 5D
HONOS: Health Nation Outcome Scale
ICER: incremental cost-effectiveness ratio
ICPT: Interpersonal Community Psychiatric Treatment
IMR: Illness Management and Recovery
MANSA: Manchester Short Assessment of Quality of Life
MHS: Mental Health Services
MINI Plus: (Mini Neuro-psychiatric Interview)
OQ45: Outcome Questionnaire45
QUALY: quality adjusted life years
SAPAS: Standardised Assessment of Personality –Abbreviated Scale, Self Report -SIDP-IV, Structured Interview for DSM-IV
SNM: Social Network Map
STAR: Scale to Assess the Therapeutic Relationship
Tic-P: Trimbos/iMTA questionnaire for Costs associated with Psychiatric Illness
